### Study design

This study utilizes a two-arm, randomized controlled trial (RCT) design to determine the effects of mISP combined with digitized MINDBODYSTRONG^©^ verses mISP alone. The SPIRIT 2013 Checklist was followed (S1 File), and the approved IRB protocol can be viewed for more detail (S2 File). The mISP and MINDBODYSTRONG^©^ are carried out individually by the participant. Nurses identified with moderate to high risk of suicide through the mISP will be randomly assigned to MINDBODYSTRONG^©^ or the attention control group (i.e., mISP alone). Depression, suicidal ideation, burnout, anxiety, post-traumatic stress, healthy lifestyle beliefs, healthy lifestyle behaviors, and job satisfaction in U.S. nurses will be assessed to determine effectiveness. The post-intervention follow-up will occur at 8 weeks, 3, 6, and 12 months. These touchpoints for follow-up were selected to assess the sustainability of the intervention’s effect over time, determine whether a booster session would be needed during the first year, and identify what month would be most appropriate to do so.

Data will be collected on two platforms: (1) the mISP and (2) REDCap–a browser-based software specifically designed for clinical and translational research. Two platforms for data collection are required as the mISP is limited in its ability to link data overtime due to the encryption. To maintain data fidelity, an additional baseline survey will be completed by the participants in REDCap after completing the initial mISP screening, and all follow-up surveys will be taken in REDcap to allow for data linking at each point for analysis. Randomization will occur via REDCap. The schedule for enrollment, interventions, and assessments are viewable in Fig 1.

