### Sample size and power analysis

A power analysis was conducted based on two-sample t-tests to compare pre- vs. postintervention means with two-tailed tests and a study-wide type I error rate of 5% to adjust for multiple comparisons from seven outcomes and four between-group pre-post comparisons per outcome. Given previous positive results with MINDBODYSTRONG©, yielding a large effect size of .98 requires a sample size of 30 (21 after accounting for 30% attrition), which would detect effects with 80%. However, given the untested nature of the electronic on-line version of MINDBODYSTRONG©, a medium effect of .5 was used to calculate a desired sample of 254, which would detect intervention effects on outcomes (depression, SI, burnout, anxiety, post-traumatic stress, healthy lifestyle beliefs, healthy lifestyle behaviors, and job satisfaction) with 80% power and study-wide type I error rate of 5%. With an expected 30% attrition, we will need a target recruitment of at least 364 nurses from the ANA to ensure an analytical sample size of 254.

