### Data analysis

We will conduct intent-to-treat analyses. Descriptive statistics will be first used to examine variable distribution, identify any data abnormality such as outliers, and summarize sample characteristics, stratified by intervention and control groups. Appropriate data transformation will be performed if needed to achieve normality. For each outcome variable, mixed-effects linear regression modeling will be used to fit the outcome as a linear function of intervention, time, intervention dose, and their interactions. Generalized linear mixed-effects regression with appropriate link function will be used if data fail the normality assumption. From the model, we will obtain estimates on the between-group difference in the change of outcome measure from baseline at each follow-up time point and estimates on the dose effect of the completed sessions in the MINDBODYSTRONG^©^ program. The model will be further extended to adjust for covariates, examine nonlinear relationships, and explore the heterogeneity of intervention effects across subgroups.

The study has seven outcomes and four between-group comparisons of pre-post changes for each outcome. Therefore, multiple testing adjustment to keep the study-wide type I error rate under 0.05 will be employed. Missing data due to attrition at longitudinal follow-up is expected. We will examine the extent and pattern of missing data, and perform appropriate multiple imputation according to missing data mechanism. The mixed-effects regression modeling allows for missing at random. This analysis will be repeated with and without multiple imputation. If missing not at random exists, pattern mixture modeling will be used instead. Sensitivity analysis will be used to examine the robustness of study findings before vs. after multiple imputation or under pattern-mixture modeling. We will use SAS 9.4 for all quantitative analysis. We will conduct two-sided tests and use Bonferroni adjusted p-values < 0.007 for statistical significance to keep the study-vide type I error rate under 0.05. Due to the conservative nature of Bonferroni adjustment for multiple testing, we will conduct sensitivity analysis using other approaches (e.g., Hommel method) [52]. Regardless of statistical significance, we will report point estimates, their precision (e.g., 95% confidence intervals), and effect sizes.

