## Discussion

The mISP plus MINDBODYSTRONG^©^ RCT will examine the efficacy of a digitized, cognitive-behavioral skill building program combined with the encrypted, de-identified screening and referral program on depression, suicidal ideation, burnout, anxiety, personal cognitive beliefs, healthy lifestyle behaviors, and job satisfaction in nurses. These are pressing issues as mental health concerns, including suicidal ideation, depression, anxiety, and burnout, among nurses are currently a public health epidemic.

Mental health concerns, including suicidal ideation, ebb and flow through the lifespan. Research shows that a prior history of suicide attempts exponentially raises the risk of future suicide attempts [55]. The use of a cognitive-behavioral skill building program is impactful because the skills that participants learn and practice can be used again with future distress. Paired with the de-identified screening and referral program, those who may not have reached out for help will have timely access to assistance that can benefit them.

If found to be effective, this combination of interventions can be scaled to assist nurses through employers and providers across the U.S. A recent meta-analysis showed that the issues with high rates of depression, anxiety burnout, and suicidal ideation in nurses are not unique to the United States but seen internationally [56]. With appropriate translation and trials, there is potential for this unique combination to have a positive effect on the lives of nurses across the globe.

Findings from this study will primarily be disseminated through publications and presentations. Any needed amendments to the study, including termination, will be handled via The Ohio State University’s Institutional Review Board.

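### The 0.007 threshold is 0.05 divided by seven outcomes, but the plan counts 28 tests and names eight outcomes, so the promised 5% study-wide error rate is not kept

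*Protocol article*

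**What the plan says.** All references are to the protocol article.

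- **Family of tests.** Data analysis: "The study has seven outcomes and four between-group comparisons of pre-post changes for each outcome". Sample size and power analysis uses the same count: "seven outcomes and four between-group pre-post comparisons per outcome".
- **What is promised.** Data analysis draws the consequence from that count: "multiple testing adjustment to keep the study-wide type I error rate under 0.05 will be employed".
- **The rule.** Later in the same paragraph, the trial will "use Bonferroni adjusted p-values < 0.007 for statistical significance to keep the study-vide type I error rate under 0.05". The Hommel method is offered as a sensitivity analysis only.
- **What is tested.** The model for each outcome yields "estimates on the between-group difference in the change of outcome measure from baseline at each follow-up time point". Study design gives four such points: "The post-intervention follow-up will occur at 8 weeks, 3, 6, and 12 months".
- **Number of outcomes.** The power paragraph says seven but lists eight: "depression, SI, burnout, anxiety, post-traumatic stress, healthy lifestyle beliefs, healthy lifestyle behaviors, and job satisfaction) with 80% power". The Aims in the abstract, the Study aim and the Study design also name eight. The Discussion names seven, leaving out post-traumatic stress: "depression, suicidal ideation, burnout, anxiety, personal cognitive beliefs, healthy lifestyle behaviors, and job satisfaction in nurses".

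**The concern.** The threshold and the family do not match. Dividing 0.05 by seven allows for one test per outcome, while the paragraph that sets the threshold says each outcome is tested four times. The count of seven is itself in doubt, because eight outcomes are named almost everywhere else.

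The wording adds a further fault. A Bonferroni-adjusted p-value is compared with 0.05, and a raw p-value with the divided alpha. Comparing an adjusted p-value with a divided alpha mixes the two.

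The article names no primary outcome and no primary time point, and it hypothesises benefit on every outcome at all four follow-ups. Any of the 28 or 32 contrasts could therefore be declared significant and read as evidence that the programme works in nurses at moderate to high suicide risk. The study-wide error rate is the only protection the plan offers against a chance finding, so a threshold that does not deliver it matters.

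**Working it through.** **Inputs from the article.** Study-wide alpha 0.05, two-sided; threshold 0.007; seven outcomes by count and eight by name; four follow-ups; d = 0.5; 254 analysed (127 per arm at 1:1 allocation); 80% power; 30% attrition; 364 recruited.

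**1. Where 0.007 comes from.** Bonferroni threshold = 0.05/m.

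| m | Meaning | 0.05/m |
|---|---|---|
| 4 | follow-ups only | 0.0125 |
| 7 | outcomes as counted | 0.00714 |
| 8 | outcomes as named | 0.00625 |
| 28 | 7 × 4 | 0.00179 |
| 32 | 8 × 4 | 0.00156 |

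Only m = 7 rounds to 0.007. The four comparisons per outcome have dropped out.

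**2. Family-wise error at 0.007 per test.** Bound = m × 0.007. Under independence, error = 1 − (1 − 0.007)^m.

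| Tests | Bound | Independence |
|---|---|---|
| 7 | 0.049 | 4.8% |
| 8 | 0.056 | 5.5% |
| 28 | 0.196 | 17.9% |
| 32 | 0.224 | 20.1% |

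The rule keeps its promise only for seven tests in total.

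**3. Allowing for correlation.** Repeated measures and related scales are positively correlated, which lowers these figures. The article gives no correlations, so those used here are assumptions. Correlated null z-statistics were simulated (400,000 draws per scenario), with equal correlation between visits of 0 to 0.9 and between outcomes of 0 to 0.7.

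| Correlation between visits / outcomes | 28 tests | 32 tests |
|---|---|---|
| 0 / 0 | 17.9% | 20.1% |
| 0.5 / 0.3 | 15.0% | 16.9% |
| 0.7 / 0.5 | 11.2% | 12.5% |
| 0.8 / 0.7 | 7.8% | 8.5% |
| 0.9 / 0.7 | 6.3% | 6.9% |

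The error exceeds 5% in every scenario, including the most strongly correlated.

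**4. Which alpha the sample size implies.** The article prints no per-test alpha, so this is a back-calculation. Normal formula: n per arm = 2(z₁₋α/₂ + z₀.₈)²/d².

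- α = 0.05/28: z = 3.124, n = 2(3.124 + 0.842)²/0.25 = 125.8, so 126 per arm and 252 in total. The t-test version gives 258. The stated 254 lies between them.
- α = 0.05/7: z = 2.690, n = 99.8, so 100 per arm and 200 in total. The t-test version gives 204.

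The attrition step reproduces: 254/0.7 = 362.9, so 363, or 364 for equal arms.

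Power of the two-sample t-test with 127 per arm and d = 0.5:

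| α | Power |
|---|---|
| 0.007 | 0.896 |
| 0.05/28 | 0.7945 |
| 0.05/32 | 0.783 |

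The stated 80% belongs with a threshold near 0.05/28. Planning and analysis differ by a factor of 0.00714/0.00179 = 4, the number of follow-ups.

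**The case against.** The best defence takes the words about adjusted p-values seriously. If each p-value is first adjusted for the four comparisons within an outcome and then compared with 0.05/7, the raw threshold is 0.007/4 = 0.00175, close to 0.05/28. The normal formula at 0.00175 gives 126.2, so 127 per arm and exactly 254. A reading therefore exists that reconciles the analysis rule with the sample size.

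This is suggestive, but the two steps are written nowhere, and nearby alphas can give the same 254. Even if granted, eight outcomes leave a bound of 32 × 0.00175 = 0.056, still above the promise. The other literal reading, p-values adjusted for all 28 tests and then held to 0.007, means raw p < 0.007/28 = 0.00025. It controls error, but power with 127 per arm falls to about 61% by the t-test, against the stated 80%. A rule that can be read three ways, with power from about 61% to 90%, has to be rewritten.

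Three further points stand in part. The 18% and 20% figures are the independence case, which is unrealistic for repeated measures; the real excess depends on unknown correlations and could be modest. The article also commits to reporting estimates, intervals and effect sizes whatever the p-value, and to a Hommel sensitivity analysis, which limits the harm without repairing the main rule. Finally, one omnibus group-by-time test per outcome, or a named primary outcome or visit, would also restore control. None is stated.

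**Conclusion.** Wrong as written. On the plain reading, 0.007 controls seven tests, while the article counts 28 and names outcomes enough for 32. The bound on the study-wide error is 0.196 or 0.224 against a promised 0.05, and the simulated error was at least 6.3% in every scenario tried. The arithmetic of the threshold and the bound needs no assumption. The simulated figures rest on assumed, equal correlations, and the link between 254 and 0.05/28 is inferred from the sample size.

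**What to change.** Replace the threshold sentence in Data analysis with wording such as: *All 32 between-group contrasts (eight outcomes at four follow-up visits) form one family. Raw p-values are tested by the Holm procedure at a study-wide two-sided 0.05, with a first-step threshold of 0.05/32 = 0.0016; equivalently, Holm-adjusted p-values are compared with 0.05.*

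Holm needs no assumption beyond Bonferroni's and is never less powerful. Hommel can stay as the sensitivity analysis. Change seven to eight in both Data analysis and Sample size and power analysis, and bring the Discussion list into line. If the authors intend only seven outcomes, they should say which one is outside the family and use 28 tests with 0.05/28 at the first step.

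The change is mainly one of wording, and the article reports that recruitment is unfinished and no results exist. It has a small cost in power. With 254 analysed, single-test power at the first Holm step is about 78% (t-test) or 79% (normal formula), and this should be stated beside the 80%. Restoring 80% at 0.05/32 would take 258 (normal) or 262 (t-test) analysed, which is 258/0.7 = 369 or 262/0.7 = 375 recruited, against the planned 364.

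### Significance is decided by single-step Bonferroni although Holm, over the same family and with the same error control, is never less powerful

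*Protocol article*

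**What the plan says.** The Data analysis section of the protocol article defines the family: "The study has seven outcomes and four between-group comparisons of pre-post changes for each outcome". It promises that "multiple testing adjustment to keep the study-wide type I error rate under 0.05 will be employed". The deciding rule is to "use Bonferroni adjusted p-values < 0.007 for statistical significance". The section then adds: "Due to the conservative nature of Bonferroni adjustment for multiple testing, we will conduct sensitivity analysis using other approaches (e.g., Hommel method". Hommel is an example only, and the list of alternatives is open. The section does not say how a disagreement between procedures would be reported. It does commit to reporting estimates, 95% intervals and effect sizes whatever the test result.

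The Sample size and power analysis section uses the same error target ("two-tailed tests and a study-wide type I error rate of 5% to adjust for multiple comparisons") and states that "a medium effect of .5 was used to calculate a desired sample of 254".

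**The concern.** A multiplicity procedure is a rejection rule. Running a second one on the same p-values varies no assumption about the data, the model or the missingness, so it is not a sensitivity analysis in the usual sense. If the plan regards its rule as too conservative, the place to deal with that is the rule itself.

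A remedy exists that costs no error control. Holm compares the smallest p-value with 0.05/m, the next with 0.05/(m−1), and so on, stopping at the first failure. Every threshold is at least 0.05/m, so whatever Bonferroni rejects Holm also rejects. Like Bonferroni, it controls the family-wise error under any dependence. At stake are real effects that the study would report as not significant when an equally strict rule would have declared them.

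**Working it through.** **Inputs.** From the article: 7 outcomes × 4 comparisons = 28 tests; study-wide alpha 0.05, two-sided; d = 0.5; 254 analysed, 1:1, so 127 per arm; 80% power; 30% attrition; cut-off 0.007. The article gives no correlations between outcomes or visits. I assume a common correlation of 0.3, 0.5 or 0.7 between test statistics.

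**The plan's sample size.** Bonferroni over 28 tests gives 0.05/28 = 0.001786, with two-sided critical value 3.124. Then n per arm = 2(3.124 + 0.842)²/0.5² = 125.8, so 126 per arm and 252 in total; the noncentral t version gives 258. The stated 254 lies between them. Recruitment: 254/0.70 = 362.9, or 364 as an even total. At 0.007 the total would be 202 (z) or 204 (t), so 254 was not sized on the written cut-off.

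**Power of single tests at 127 per arm.** The expected statistic is 0.5 × √(127/2) = 3.984.
- At 0.05/28: Φ(3.984 − 3.124) = 0.805.
- At 0.007 (critical value 2.697): Φ(3.984 − 2.697) = 0.901.

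**Holm against Bonferroni on the same family.** Simulation of 40,000 trials per setting: equicorrelated normal statistics, mean 3.984 where an effect is real and 0 otherwise. Entries are average power per real effect.

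| Family | Real effects | Bonferroni at 0.05/m | Holm, correlation 0.3 / 0.5 / 0.7 |
|---|---|---|---|
| 28 | 14 | 80–81% | 84.1 / 83.9 / 83.2% |
| 28 | 28 | 80–81% | 92.4 / 91.0 / 89.6% |
| 7 | 3 | 90% | 91.7 / 91.8 / 91.4% |
| 7 | 7 | 90% | 96.6 / 95.9 / 95.2% |

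In no simulated trial did Bonferroni reject a test that Holm did not. With 14 of 28 effects real, Holm's family-wise error was 2–4%.

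**The written cut-off.** 0.05/7 = 0.00714, so 0.007 fits seven tests. Against 28 it is 0.007/0.001786 = 3.9 times too lenient. With all 28 nulls true, the family-wise error is at most 28 × 0.007 = 0.196; it is 1 − 0.993²⁸ = 0.179 under independence, and about 7% (correlation 0.7) to 14–15% (correlation 0.3) in simulation. Its power per test is about 90%. Moving from 0.007 to Holm over 28 therefore changes power from about 90% to about 84% if half the effects are real, and leaves it at about 90–92% if all are.

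**Illustration.** Take 28 tests with one p = 0.005 and the rest 0.3. The 0.007 rule declares significance. Holm's smallest adjusted p-value is 28 × 0.005 = 0.14, so it declares none.

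**The case against.** *One decider is named.* A reader might infer two competing primary rules with nothing to settle which counts. The article does not support that: Bonferroni decides, Hommel is labelled sensitivity analysis, and nothing lets a Hommel result replace the main verdict. What remains is that the list of alternatives is open and the reporting of a disagreement is unstated. That is minor, and the analysis plan may settle it.

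*Bonferroni is valid and the sample size already pays for it.* True: 254 delivers about 80% at 0.05/28, so planned power is met. Holm adds power at the same sample size and the same error guarantee, so meeting the target is no reason to forgo it.

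*Hommel needs independence or a form of positive dependence.* This is a fair reason not to make Hommel the decider. It does not apply to Holm.

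*The written rule is lenient, not conservative.* Correct for 28 tests. A reader might infer that the plan as written gives power away. Against 0.007 it does not; the loss exists only against a Bonferroni rule that delivers the promised 5%.

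*The large gains need every effect to be real.* Also correct. Under correlation 0.5, power to show all 28 effects rises from 24% to 73%, but that requires d = 0.5 on every outcome at every visit to 12 months. The study hypothesis does claim benefit throughout, but the half-real rows are the more cautious guide.

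*Bonferroni gives matching simultaneous intervals more easily.* The plan reports ordinary 95% intervals regardless of significance, so nothing it promises is lost.

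**Conclusion.** The point holds as an efficiency gain at no cost in error control; it is not an error of validity. Measured against Bonferroni at the correct level for the family, Holm adds about 3 to 4 percentage points of power per test over 28 tests if half the effects are real and about 9 to 12 if all are; over 7 tests it adds about 1 to 2 points (three real) or 5 to 6 (all real). That Holm is never less powerful on the same family and alpha is a mathematical fact. The sizes rest on d = 0.5 for every real effect, 127 analysed per arm at every visit, and assumed equal correlations of 0.3 to 0.7.

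The comparison must not be made with 0.007. Over the 28 declared tests that cut-off does not keep the promised 5%, and replacing it with Holm over 28 restores error control at a possible cost in power.

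**What to change.** State one rule: a comparison is significant when its Holm-adjusted two-sided p-value, computed over the whole declared family (outcomes × four visits), is below 0.05. Delete the 0.007 Bonferroni cut-off. This also removes the reading in which already adjusted p-values are compared with 0.007, which would adjust twice. Report Hommel or any other procedure as supportive only, unable to change a conclusion.

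The number of outcomes has to be settled in the same edit: seven are counted, but eight are named ("depression, SI, burnout, anxiety, post-traumatic stress, healthy lifestyle beliefs, healthy lifestyle behaviors, and job satisfaction"), which would make 8 × 4 = 32 tests.

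The cost is a sentence or two. Sample size and data collection do not change, and the adjustment is available in standard software. All tests in the family must be run before any is declared significant. The article states that recruitment was still under way and no results had been generated, so as of that statement the rule could be changed without knowledge of results.

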### Safety and risk considerations

Participants may acquire valuable information about their personal health and wellness that they may use in their future by consenting to the study. The surveys, screeners, and assessments selected for this study pose minimal risk to participants. However, the surveys, screeners, and assessments may result in uncomfortable emotions for the participant. Thus, a Data and Safety Monitoring Plan and Board have been established for this study to protect the health and safety of participants and provide information relevant to their participation. Participants will also be provided with a set of mental health care resources.

At the time of consent, participants are made aware that the mISP program and the corresponding study are not crisis response services, and that immediate availability of the therapist should not be expected. Participants identified as having moderate to high risk of suicide will be contacted via the encrypted mISP program within 24 hours during the work week, however there is no guarantee that the therapist will be available to address any safety concerns before then, including imminent suicide risk or other mental health crisis. The therapist, facilitation, and investigators will make best efforts to assist the participants with tools, resources, and referrals to protect themselves in crisis situations, but it is dependent on the participants to interact with study personnel and follow through to keep themselves safe.

The information shared by the participants and the data compiled is collected and stored online; therefore, there is a potential risk of data breach. AFSP has created an individualized version of the mISP specific to this study to assist in protecting the data acquired within the mISP. AFSP will maintain the encryption of the mISP program so that communications between the participant and therapist are protected, and the identity of the participant is kept private.

